##### Cost-Utility: Cost Units

Since the study intervention is home-based, the intervention will have no direct impact on societal costs, such as travel expenses or the time spent by the caregiver at home, but the possible reduction of health visits to physician or nursery could vary. However, variation in travel costs (time and transport) of the initial visit to participants’ homes to explain the study and to evaluate the caregivers will be included in the sensitivity analysis. The economic analyses will be performed from a health service perspective, as recommended by the National Institute for Clinical Excellence (NICE) in the UK to inform decisions concerning health-care policy for an expensive condition. This may help to determine whether the addition of the program to the health system should be funded. The unit costs will be expressed in Euros (€) in the current year of intervention.

No adjustment will be required for changes in currency value over time, as the study will focus on effects observed over a period of ≤1 year. The costs of the program will be calculated on the basis of: university graduate salary levels; personnel costs for the running of the program; public-sector mileage rates; and the private external management costs of the program (insurance, basic portable sport materials, e.g., strings and step-equipment). Health-care prices (consultations, etc.) will be based on the official bulletin of the regional government of Extremadura. Drug prices will be obtained from the Spanish version of the Vademecum International [79].

#### 3.1.2. Subjective Burden

Participants will be also assessed using the Zarit Carer Burden Interview (ZBI) [80]. This 22-item self-report questionnaire examines the burden experienced by caregivers according to a rate scale which ranges from 0 to 88, where 0 indicates no burden and 88 indicates severe burden. The questionnaire addresses the functional, psychological, behavioral, and economic difficulties associated with the home care situation.

#### 3.1.3. Depression

Risk for depression will be assessed using the Short Form 15-item version of the Geriatric Depression Scale [81]. This 15-item self-report questionnaire is a reliable screening-tool for late-life major depression in the primary care setting. Scores range from 0 to 15. The presence of ≥5 symptoms indicates possible depression [82].

#### 3.1.4. Psychological Symptomatology

Psychological symptomatology will be measured using the Symptom Check List-90-R (SCL-90-R) [83]. This 90-item self-report questionnaire assesses the presence of psychological distress and a range of psychopathological symptoms. In particular, the SCL-90-R yields scores for nine primary symptom dimensions: somatization, obsessive-compulsive disorder, interpersonal sensitivity, depression, anxiety, hostility, phobic anxiety, paranoid ideation and psychoticism, as well as three indices of global distress. Each item is scored according to a 5-point Likert scale, which ranges from 0 = not at all to 4 = extremely. If the resulted global severity index is greater than or equal to a T score of 63th percentile or if the scores of two of those dimensions are greater than or equal to a T score of 63 or 75th percentile, this means that the respondent experiences severe symptomatology (positive case for caseness) [83].

#### 3.1.5. Fitness

Weight, height, and the circumference of the waist and hip will be assessed according to the recommendations established by the European Council [84] for the calculation of body mass index (BMI) and waist / hip ratio (WHR).Handgrip strength will be assessed in both hands using a hand dynamometer (TKK; Tokyo, Japan). The mean value for the two hands will be used as the final outcome.Lumbar trunk muscle endurance will be assessed using two tests [85]. To evaluate flexor endurance, the subject will be asked to lie in a supine position and to raise the lower extremities with 90° flexion of the hip and knee joints. To evaluate extensor endurance, the subject will be asked to lie in a prone position while holding the sternum off the floor. During both procedures, the subject will be asked to maintain the original positions for as long as possible but without exceeding a 2-min time limit.Flexibility will be measured using the sit-and-reach test [86]. During this trunk flexion exercise, the distance between the tips of the fingers at the start and final positions will be recorded. The best result of three trials will be used as the outcome.Postural balance will be evaluated using the blind flamingo test [87,88,89]. Here, the barefoot subject stands on one leg with his/her eyes closed, while the other leg is flexed at the knee and held at the ankle by the hand of the same side. The chronometer is stopped whenever the subject does not comply with the protocol conditions. The number of trials required to remain static in this position for 30 s is measured. The outcome is expressed as the number of trials (=number of falls + 1).Lower extremity function will be assessed using the chair-stand test [90]. The subject sits in a standardized chair (0.43 m in height). The subject is asked to stand upright with his/her arms folded across the chest and then sit back down again. This is repeated 10 times, as quickly and as safely as possible. The best result of two trials (expressed in s) separated by 3 min is used as the outcome.

### 3.2. Secondary Outcomes

#### 3.2.1. Exercise Adherence

Each participant in the intervention group will be prescribed a total of 72 exercise sessions. Completion of the sessions across the 9-month-long intervention will be monitored by the supervising personal trainer. Exercise adherence rates during the intervention will be calculated as the percentage of the 72 prescribed exercise sessions.

#### 3.2.2. Potential Adverse Effects of the Intervention

Although it has been previously well documented that interventions that are based on physical exercises are beneficial for health, as this exercise program is provided at caregivers’ homes, the following potential adverse effects of the intervention have to be taken into account. First, physical harm or injuries. In this case, if the participant is severe injured, the personal trainer will recommend the caregiver to visit the doctor. If the caregiver is not able to continue the intervention because of the injury, he or she should withdraw the intervention. Second, caregivers may feel resentful while carrying out the physical exercises. Finally, the session of physical exercise might be interrupted because of caregivers’ behaviors.

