Although the role of caregiver may be perceived as satisfying and rewarding [9], the progressive and protracted deterioration of the state of health of individuals with dementia [8,10] requires caregivers to provide them with continuous support in all areas of life for long periods of time [11]. Moreover, the exact length of these long periods, as well as all the things that may happen to the subject with dementia, is usually unknown by informal caregivers. As a consequence, the exercise of the role of the caregiver leads to a wide variety of physical, psychological, social and financial difficulties [7,12,13,14,15]. In this regard, the adverse effects on physical health and quality of life are diverse [16,17,18,19,20]. Informal caregivers show higher rates of hypertension and other cardiovascular-related disorders [21,22], as well as lower aerobic endurance [23] than non-caregivers. Informal caregivers have reported having severe back pain due to alterations in the trunk muscle extensor strength [8,20], and other osteomuscular disorders [4]. At the psychological level, it has been found that informal caregivers experience high levels of subjective burden, distress, and a wide variety of psychological disorders [5,13,21,24,25,26,27,28,29], as well as sleep problems [30,31,32]. In addition, as part of their role, caregivers also suffer other symptoms such as hostility, aggression, somatization, irritability, hallucinations, delusions, restlessness, and disinhibition [2,33,34,35]. Regarding social and financial troubles, informal caregivers usually expend the most of their time and economic resources in providing the patient with care; this leads to a reduction in leisure activities [5] and, probably, to social isolation. Accordingly, the quality of life of informal caregivers of patients with dementia is also seriously affected [26].

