### 2.3. Intervention

The 9-month-long intervention, which will be an additional intervention to the conventional care provided by the public health system, as previously described, will include 2 home-based physical exercise 1-hour-long sessions per week for caregivers of relatives with dementia. These physical exercise sessions will be supervised by a physical trainer, who will have an academic degree in sport sciences, and who will be blind to the results of the assessments. Each session will be of home-based, individual and face-to-face nature. While the physical trainer and caregiver are performing the exercise session, the patient might stay at home, either sitting-down doing easy tasks (e.g., watching TV or playing with a pencil and paper-drawing or game task) or carrying out a craft that would be suitable for his/her level of deterioration.

The physical exercise intervention basically consists of aerobic exercises of moderate intensity, which means about 3 to 6 metabolic equivalents. In particular, each physical activity session will consist of: (1) 10-minutes-long warm-up activities that include slight movements of progressive intensity and easy walks and steps. (2) This will be followed by 10-minutes-long aerobic exercises at 60%–65% of maximal heart rate (HR_max_), which will be followed by 20-minute-long overall mobility and strength exercises using own body weight and other materials, which will be followed by a further 10-minute-long aerobic exercise at 60%–65% HR_max_, which will be finally followed by a 10-minute-long cool-down period that includes low-intensity exercises for participants to reach s state of calm.

In order to enhance the attractiveness and the positive effects of the exercises, supplementary materials, such as weights, dumbbells, and elastic bands will be used. During each physical activity session, participants’ heart rate will be monitored by means of a so-called individual running computer (Polar S625X, 1 Polar Electro Oy, Kempele, Finland).

During the 9-months-long intervention, and in order to reinforce other healthy habits in their daily lives apart from physical exercise, participants of the intervention group will be sent a health-counselling document once a month, in which the importance of the following issues will be addressed: adequate rest, safe positioning of the back during caring activities, and regular participation in daily social activities.

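### Adverse effects are a listed secondary outcome but are described only for the exercise sessions, so injury and musculoskeletal event counts would have no control-arm comparator

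*Protocol article*

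**What the plan says.** Section 3.2 of the protocol article has two secondary outcomes: exercise adherence (3.2.1) and potential adverse effects of the intervention (3.2.2). The second is introduced by saying that, because the programme is delivered at home, "the following potential adverse effects of the intervention have to be taken into account". Three effects follow.

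- **Injury.** Two actions are stated: "if the participant is severe injured, the personal trainer will recommend the caregiver to visit the doctor", and "If the caregiver is not able to continue the intervention because of the injury, he or she should withdraw the intervention".
- **Resentment.** "Second, caregivers may feel resentful while carrying out the physical exercises".
- **Interruption.** "the session of physical exercise might be interrupted because of" the behaviour of the caregivers.

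Section 2.3 places the trainer in the exercise arm only: "These physical exercise sessions will be supervised by a physical trainer". For controls, the same section describes a standardized telephone conversation once a month, unrelated to exercise, whose stated purpose is to remind them of the study conditions.

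Section 2.4 has trained evaluators visit both groups at home at baseline and at the 3-, 9- and 12-month assessments. On background complaints, the Introduction says: "Informal caregivers have reported having severe back pain", and it mentions other musculoskeletal disorders as well.

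**The concern.** A harm outcome in a randomised trial is interpretable when the same events are sought in the same way in both arms. Section 3.2.2 instead describes the outcome by its supposed cause, as something that exercise sessions produce. Following that text gives a count of injuries in the exercise arm and nothing to subtract from it.

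That matters in this population. Women aged 50 or over who give at least 20 hours of care a week, in a group said to have back pain already, will report some strains and pain flare-ups whether or not they exercise. Without a control count, a modest number of events could be read as harm when it is background, or dismissed as background when it is harm. The Discussion says that the results could inform policymakers on home-based services, so a reader will want to know whether the programme injures people.

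Information on controls that is not collected during the trial cannot be recovered at analysis.

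**Working it through.** The article gives no adverse-event rate, margin or power, so there is no figure to reproduce. The check sets the relevant sections side by side and then sizes what equal enquiry could deliver.

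**1. Which listed effects could occur in a control?** Resentment while exercising and interruption of a session cannot. Injury can, and so can new or worsened musculoskeletal pain. The comparator problem is therefore confined to injury and musculoskeletal events.

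**2. What is described for each arm?**

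| | Exercise arm | Control arm |
|---|---|---|
| Person named for injuries (3.2.2) | Personal trainer | None |
| Regular contact (2.3, 3.2.1) | 72 supervised sessions | Monthly call for 9 months, about 9 |
| Injury or pain enquiry described | Trainer's response to injury | None |
| Evaluator visits (2.4) | Baseline, 3, 9, 12 months | The same |

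Contact frequency: 72 / 9 = 8 times as many contacts in the exercise arm. Adding a question to both the session log and the call would not make observation equal. The only symmetric contacts are the evaluator visits.

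**3. What do the measures shared by both arms supply?**

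- EQ-5D-3L (3.1.1): a mobility item and a pain/discomfort item with three levels each, at visits months apart. They show net status, so an expected improvement can hide a strain or injury.
- SCL-90-R (3.1.4): a somatization score, not an event record.
- Health-service use (2.4.2): hospital stays, medication and appointments during the 9 months, with no restriction to one arm. It misses injuries that lead to no care. The trainer's advice to see a doctor may also raise appointments in one arm, since no counterpart is described for controls.

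All three allow an indirect comparison. None counts injuries or attributes a cause.

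**4. What would equal enquiry deliver?** Inputs: N = 50 and 20% dropout (2.2.1). Equal allocation and the event rates are assumptions. Two-sided 5% level, n per arm, p̄ the mean of p1 and p2:

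power = Φ{ [ |p2 − p1| − 1.96 √(2 p̄(1 − p̄)/n) ] / √( [p1(1 − p1) + p2(1 − p2)]/n ) }

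For 10% against 30% with n = 25: √(2 × 0.2 × 0.8/25) = 0.1131 and √((0.09 + 0.21)/25) = 0.1095, so power = Φ[(0.2 − 1.96 × 0.1131)/0.1095] = Φ(−0.20) = 42%.

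| Assumed rates | 25 per arm | 20 per arm |
|---|---|---|
| 10% vs 30% | 42% | 35% |
| 5% vs 15% | 21% | 18% |

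The normal approximation is rough at such small counts, but the message is clear: equal enquiry supports a descriptive table, not a powered test.

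**The case against.** The strongest reply is that this is a journal article. Event definitions, question wording and logs commonly sit in the full protocol, so their absence here shows nothing. That stands, and the point does not rely on it. It rests on what section 3.2.2 does state: a listed outcome framed as effects of one arm's sessions.

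Three stronger readings are tempting and should not be adopted.

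- A reader might infer that only the trainer sees adverse effects. The article does not say so. It names the trainer for the advice to see a doctor and is silent on who records events. Likewise, it does not state that controls are never asked; it describes no such enquiry.
- A reader might infer that action is stated only for severe injury. The next sentence covers withdrawal from the intervention when an injury prevents continuing, and it is not tied to severity. Nor does it remove anyone from follow-up assessments. Whether these rules suit clinically is outside this point.
- A reader might conclude that the trial cannot tell exercise harm from background complaints at all. The shared measures do give some control-arm information, so that is too strong.

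Two further arguments should also be set aside. With zero events in 25 participants, the one-sided 95% upper limit is 1 − 0.05^(1/25) = 11.3%. That follows from the sample size alone and would be the same with perfect two-arm capture, so it does not show the defect. And section 2.3 says that "the patient might stay at home, either sitting-down doing easy tasks", while section 3.2.2 attributes interruptions to caregivers. This may be a slip for care recipients. It is a wording query, and it does not establish that incidents involving the relative are excluded from an illustrative list.

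**Conclusion.** The point holds in limited form. Adverse effects are a secondary outcome described only for the exercise sessions, with the trainer the only person named and no matching enquiry described for controls. If the trial follows this text, injury and musculoskeletal event counts could not be compared between arms, in a population for which the article itself reports background back pain. The shared pain, somatization and health-service data soften the gap but do not close it, because they are indirect and do not count events.

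The defect does not touch the primary outcome or the cost-utility analysis plan. Correcting it would yield a descriptive comparison with, for example, about 42% power for 10% against 30% at 25 per arm (equal allocation and these rates being assumptions). It is a cheap improvement worth making before data collection. If the full protocol already has a symmetric enquiry, the article need only say so.

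**What to change.** 1. For the part of the outcome that can occur in either arm, define it as any injury, any fall, and new or worsened musculoskeletal pain since the previous visit, whatever the supposed cause.
2. Have the evaluators ask one identical closed question on this in both arms at the existing 3-, 9- and 12-month visits.
3. Report the number of participants with at least one event by arm, labelled as a descriptive comparison.
4. Report trainer-logged session events, including interruptions, separately for the exercise arm. Do not use them for the between-arm comparison, because contact frequency differs (72 sessions against about 9 calls).
5. Check whether the interruption sentence in section 3.2.2 means caregivers or the relatives in their care, and reword it if needed.

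The cost is about a minute per visit and one summary table; the monthly control call stays as it is. Two limits remain. Participants know their arm, and recall runs over several months between visits, so answers may be incomplete. With about 25 per arm, only a large difference would stand out.

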## 4. Discussion

The provision of care to individuals with dementia is an unforeseen task that involves great efforts and represents a daily challenge for caregivers. This situation adversely impacts the physical, psychological, social, and financial well-being of caregivers [7,12,13,14,15]. In this sense, anxiety, depression, and subjective burden, and a multitude of other symptoms have been reported [2,5,13,24,28]. In addition, caregivers also show lower levels of fitness and higher rates of other physical disorders than non-caregivers [8,20,21,23]. As a consequence, this overburdened daily situation results in harmful effects on physical health and health-related quality of life [16,17,18,19,20] for caregivers. Hence, tailored interventions aiming to improve the health status of this population are warranted, as it is an important demand of society [36,37]. The health-related quality of life consists of several dimensions (e.g., mobility, self-care, doing daily activities, pain or discomfort and anxiety or depression) according to the EQ-5D-3L instrument described in methods. This health-related quality of life is worst in this population [20], especially in pain/discomfort, anxiety/depression and other psychological symptoms such as somatization, hostility or obsession-compulsion [91]. The intervention described in this article has been conceived to provide the targeted caregivers with a suitable support program aiming to improve the health-related quality of life, in response to the difficulties, such as lack of leisure-time or financial difficulties [58,92] that they usually have when it comes to participate in conventional exercise activity programs. Moreover, in order to increase the adherence to the intervention, it will be individually tailored, as previous research recommends [42]. In particular, the sessions will be provided at each caregiver’s home, and both the intensity and the types of the exercises will be adapted to each caregiver’s fitness level. Moreover, it is considered that the method of this study is robust and adequate to evaluate the effect of the intervention on family caregivers.

In the scientific literature, there is a wide range of supporting interventions for caregivers of relatives with dementia. According to this previous research, physical exercise interventions are considered as useful and feasible nonpharmacological strategies to improve the physical and psychological health of those caregivers [43,52,60]. However, there is a lack of tailored home-based physical exercise programs for such caregivers in Spain. Therefore, to the best of our knowledge, this is the first home-based physical exercise intervention that uses a controlled trial approach in this country for informal caregivers of relatives with dementia. 

On the other hand, several previous studies have suggested the implementation of home-based interventions, since these are considered as more effective in improving quality of life and reducing levels of distress [93]. The fact that an RCT approach will be used will enable us to provide scientific evidences on the efficacy and cost-effectiveness of a home-based physical exercise intervention to improve fitness and health-related quality of life for informal caregivers of patients with dementia. In addition, the outcomes of the present intervention could provide evidences for policymakers to strengthen home-based interventions health policies that might have implications to lessen the investments of financial resources in hospitalizations, health services and the intake of medication.

We are also interested in evaluating the cost-effectiveness of the physical exercise program on the whole health of caregivers. In this sense, the most widely used methodological approach is to measure the consequences in terms of quality-adjusted life years (QALYs) that will be gained by the caregivers after the intervention, because it can combine gains in quantity of life and gains in quality of life in a single metric [94]. For this reason, we have selected the EQ-5D-3L, a well-known tool for evaluating the cost utility of the targeted intervention. Additionally, as we have previously described, several standardized measures will be also used to assess fitness, health-related outcomes, and psychological symptoms among participants. These variables have been selected because, according to the available scientific literature, several previous research studies have frequently documented that informal caregivers usually report lower scores than other populations in fitness, health-related quality of life and psychological wellbeing [20,24,29,92]. This will generate feasible data concerning the effectiveness of the intervention for caregivers. In this regard, and according to previous research [58], it is expected that there will be an improvement on health-related quality of life, and an increase in fitness level, as well as a decrease of burden and psychological symptoms in the caregivers subjected to the present intervention. In fact, potential indirect positive effects could be reported for the care recipients [58], due to the improvements of their caregivers.

If the present study protocol contributes to confirming the effectiveness of the intervention for informal caregivers of relatives with dementia, this study protocol and the research study proposed here might be applied to other caregiver populations such as family caregivers of relatives with Parkinson’s Disease, stroke, cancer or even to caregivers who do not reside with the care-recipient, such as neighbors or friends.

Finally, we have to point out the main limitation of the present study. We are referring to the relatively small sample size, which may limit the generalization of the results to other contexts. However, the sample size is adequate for assessing the effectiveness of the targeted intervention, and future research efforts will have to determine the required adjustments for future studies, larger cohorts or other populations.

